## 4. Study assessment

### 4.1 Rate of radiotherapy interruption assessment

The primary endpoint was the radiotherapy interruption rate. Radiotherapy interruption was defined as actual radiotherapy days minus planned radiotherapy days greater than or equal to 5 days, regardless of the causes for interruption. The radiotherapy interruption rate was calculated as the proportion of individuals in each group who experienced such a delay. Weekends and statutory holidays were counted into the planned radiotherapy schedule.

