➤ **Intervention Strategies**

● **Anti-Cancer Treatment Regimen**

All enrolled patients received radiotherapy delivered in daily fractions of 1.8 - 2.2 Gy, administered five times per week for 6 - 6.5 weeks, resulting in a total tumor dose of 60 - 72 Gy. The clinical target volume and organs at risk were delineated in accordance with consensus guidelines. Concurrent chemotherapy consisted of cisplatin 100 mg/m^2 every 3 weeks.

● **Intervention Measures for the Usual Care Group**

In the control group, based on the patients' questionnaire results, the radiation oncologist and risk-stratified nurses would provide dietary or psychological guidance or recommend appropriate outpatient clinics (nutrition, psychology, or rehabilitation) for patients to seek further consultation. Patients had the autonomy to decide whether or not

to schedule appointments at the recommended outpatient clinics. This reflects the routine medical practice commonly experienced by patients undergoing radiotherapy in China.

- **Intervention Measures for the SHINE-MDT Group**

In the experimental group, patients would be treated with SHINE-MDT in addition to standard anti-oncologic treatment. The SHINE-MDT model with a fixed-site and fixed-membership organizational framework. The team consisted of specialists from radiation oncology, medical oncology, psychology, nutrition, rehabilitation, and nursing, with each discipline maintaining  $\geq 3$  core members. At least one representative from each key department attended every meeting. This team provided direct and prompt nutritional, psychological, and rehabilitation interventions tailored to the patient's needs. All departments participated consistently, facilitating mutual learning and collaborative decision-making.

- **Questionnaires Assessments**

Assessments were conducted through a series of questionnaire surveys, which included the European Organization for Research and Treatment of Cancer (EORTC) Quality-of-life Questionnaire Core 30 (EORTC QLQ-C30) and Head and Neck Cancer Module (EORTC QLQ-H&N35), NRS 2002, PG-SGA, DT, PHQ-9, and HADS. The PHQ-9 and HADS were evaluated every two weeks from radiotherapy initiation through the first-month post-treatment, while the other questionnaires were assessed weekly.

- **Frequency of Questionnaire Assessment**

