Assessments were conducted at baseline (pre-radiotherapy) and weekly from radiotherapy initiation through the first-month post-treatment, followed by evaluations at 2, 3, and 6 months post-treatment.

**The end of radiotherapy:** The completion of radiotherapy is the final radiotherapy day, with administration permitted within a  $\pm 1$ -day.

**The middle of radiotherapy:** The middle of radiotherapy refers to the treatment period scheduled around half of the radiotherapy schedule, within  $\pm 1$  day. Additionally, if a

patient experiences an interruption in treatment before the scheduled middle evaluation, the timing of this intermediate assessment will be delayed accordingly.

**The post-treatment surveillance:** Post-radiotherapy follow-up visits at 1, 2, 3, and 6 months after treatment completion refer to assessments conducted within a window of  $\pm$  3 days relative to the specified monthly intervals.

eTable 1: Frequency of Questionnaire Assessments

| Test Item                                               | Testing Time Points                                                                                                                                                                     |
|---------------------------------------------------------|-----------------------------------------------------------------------------------------------------------------------------------------------------------------------------------------|
| Compliance with Radiotherapy                            | At the end of radiotherapy                                                                                                                                                              |
| EORTC QLQ-C30 Core Quality of Life Questionnaire        | Baseline (pre-radiotherapy) and weekly from radiotherapy initiation through the first-month post-treatment, followed by evaluations at 2, 3, and 6 months post-treatment.               |
| EORTC QLQ-H&N35 Head and Neck Cancer Specific Module    | Baseline (pre-radiotherapy) and weekly from radiotherapy initiation through the first-month post-treatment, followed by evaluations at 2, 3, and 6 months post-treatment.               |
| Nutritional Risk Screening Tool (NRS-2002)              | Baseline (pre-radiotherapy) and weekly from radiotherapy initiation through the first-month post-treatment, followed by evaluations at 2, 3, and 6 months post-treatment.               |

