## 6. Statistical Analysis

### 6.1 Determination of Sample Size

Based on literature reports and clinical experience, the radiotherapy interruption in the control group is approximately 25%, while it was expected to be 10% in the experimental group. With a significance level ( $\alpha$ ) set at 0.025 (one-sided) and a power ( $1-\beta$ ) of 0.8, an overall predicted dropout rate of 5%, and a required sample size of 214 participants, with each group consisting of 107 participants.

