### 6.2 Statistical Analysis Population

#### ➤ ITT (Intention-to-Treat) Set:

This includes all randomized participants in the treatment groups, regardless of whether they completed the treatment or adhered to the protocol. The analysis is based on the initial group assignment to reflect real-world scenarios.

➤ **FAS (Full Analysis Set):**

This includes all participants who received the study intervention (questionnaire assessments and radiotherapy). The analysis was conducted according to the initial randomization group but may account for deviations from the protocol.

➤ **PPS (Per-Protocol Set):**

This includes only those participants who completed the study according to the protocol. The analysis strictly follows the randomized groups and is typically used to assess the treatment effect under ideal conditions.

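### The primary-endpoint rule scores a patient who stops radiotherapy early and for good as having no interruption, unless earlier gaps pushed the last fraction at least 5 days past the planned end

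*Protocol*

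**What the plan says.** Section 4.1 of the protocol sets the primary event as "actual radiotherapy days minus planned radiotherapy days greater than or equal to 5 days, regardless of the causes for interruption". The rate is "calculated as the proportion of individuals in each group who experienced such a delay". The same section adds that "Weekends and statutory holidays were counted into the planned radiotherapy schedule", which points to a count in calendar days.

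Section 3.2 describes radiotherapy as "administered five times per week for 6 - 6.5 weeks". Under the frequency of questionnaire assessment it says: "The completion of radiotherapy is the final radiotherapy day". Section 6.2 keeps all randomized patients in the ITT set "regardless of whether they completed the treatment or adhered to the protocol". The withdrawal criteria in section 3.2 carry no outcome rule.

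For planning, section 6.1 takes the control rate as 25% and says "it was expected to be 10% in the experimental group". It does not say whether either rate includes patients who never finish radiotherapy.

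**The concern.** The rule measures how far a course overran its plan. It does not ask whether the course was completed. A patient who receives every fraction but ends 5 days late is a failure. A patient who gives up halfway has a negative difference and is a non-event, and the earlier the stop, the more negative the difference.

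This matters because the background section justifies the trial by the loss of tumor control when radiotherapy is interrupted, and it names poor nutrition and distress as the main causes. Permanent stopping for those causes is the extreme form of the outcome the intervention is meant to prevent. If stopping differs between arms, the primary comparison shifts for a reason that has nothing to do with benefit, and the arm with more stoppers gains.

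**Working it through.** **Inputs.** From the protocol: the 5-day threshold (section 4.1), five fractions per week (section 3.2), and 25% vs 10%, one-sided alpha 0.025, power 0.8, 5% dropout and 107 per arm (section 6.1). Assumptions: courses of 30 or 33 fractions, a Monday start, and all rates of permanent stopping.

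**The plan's own figure.** The pooled two-proportion formula without continuity correction is

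n = [1.960 × √(2 × 0.175 × 0.825) + 0.842 × √(0.25 × 0.75 + 0.10 × 0.90)]² / 0.15², which rounds up to 100 per arm.

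With 5% dropout, 100 / 0.95 = 105.3, so 106 per arm and 212 in total. The stated 214 is close to this and is not in question here.

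**The rule applied to early stops.** Fraction f falls on calendar day 7 × ⌊(f - 1)/5⌋ + ((f - 1) mod 5) + 1. Fraction 30 is day 40, fraction 33 is day 45 and fraction 20 is day 26. Actual minus planned days for a permanent stop with no earlier gap:

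| Last fraction given | Calendar day | Planned 30 (40 days) | Planned 33 (45 days) |
|---|---|---|---|
| 10 | 12 | -28 | -33 |
| 15 | 19 | -21 | -26 |
| 20 | 26 | -14 | -19 |
| 25 | 33 | -7 | -12 |

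All are below +5, so all are non-events. To score as an event, a patient stopping after fraction 20 of 33 would need 45 + 5 - 26 = 24 days of gaps beforehand.

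**A 7-day gap followed by dropped final fractions (planned 33).**
- Drop one: fraction 32 moves to day 44 + 7 = 51, and 51 - 45 = +6, an event.
- Drop two: fraction 31 moves to day 43 + 7 = 50, and 50 - 45 = +5, an event.
- Drop three: fraction 30 moves to day 40 + 7 = 47, and 47 - 45 = +2, a non-event. Dropping more gives a smaller difference still.

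**Power if 25% and 10% include stops that the rule misses.** The observed rate is the planning rate minus the missed stops. Power is by exact binomial enumeration of the pooled z test, one-sided 0.025, 107 per arm.

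| Missed stops, control / experimental (points) | Observed rates | Power |
|---|---|---|
| 0 / 0 | 25% vs 10% | 0.84 |
| 5 / 0 | 20% vs 10% | 0.55 |
| 5 / 2 | 20% vs 8% | 0.74 |
| 2 / 2 | 23% vs 8% | 0.88 |
| 5 / 5 | 20% vs 5% | 0.94 |
| 2 / 5 | 23% vs 5% | 0.98 |

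**Power if 25% and 10% count delays only and stops are then added as events.** Normal approximation at 101 evaluable per arm (107 × 0.95 = 101.65, rounded down), where the planned rates give 0.81. Adding 2/2 points gives 27% vs 12% and 0.77. Adding 5/5 gives 30% vs 15% and 0.73. Adding 5/2 gives 30% vs 12% and 0.89. Adding 2/5 gives 27% vs 15% and 0.55.

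**The case against.** The strongest reply is that the protocol never says a non-completer counts as a success. Section 4.1 speaks of a delay and does not spell out the actual number of days for a course that is never finished. Section 6.2 does not say which set serves the primary endpoint. Section 6.1 allows 5% dropout, so some stoppers might be treated as dropouts. Such handling is often left to the SAP, which is not at hand. The sentence on completion in section 3.2 sets a questionnaire window, and eTable 1 lists radiotherapy compliance at the end of radiotherapy.

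Part of this stands. The questionnaire window is weak support, and a SAP could add a rule. But a patient who stops treatment has a known last radiotherapy day, so the outcome is not missing: the subtraction gives a definite result below 5. A SAP that scored such a patient as an event would depart from the definition in section 4.1. The compliance item has no scoring rule. The phrase on causes covers why a delay arose and does not turn a negative difference into an event.

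A second reply is that scoring stops as events makes a delay endpoint a composite. That is fair, and it is a real cost of the fix.

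A reader might also infer that the rule necessarily costs power or favors SHINE-MDT. The documents support neither. They give no stopping rate by arm, and the tables above show power moving both ways.

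**Conclusion.** The point holds for permanent stops whose last fraction does not fall at least 5 days after the planned end. For those patients the definition as written gives the wrong classification, however rare they are. It is a fault in what section 4.1 fixes for the primary endpoint, so it should be corrected.

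It should not be read as saying that every early stopper escapes. Long earlier gaps still make an event, as does a 7-day gap with only one or two final fractions dropped in the 33-fraction example. Nor does it show that the sample size is wrong.

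The size and direction of bias are unknown. The range of 0.55 to 0.98 against 0.84 rests on assumed stop rates of 0 to 5 points per arm and on the premise that 25% and 10% include the missed stops. If those rates describe delays only, the written rule loses nothing against the planned power, but the misclassification remains.

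**What to change.** In section 4.1, define the event as: the full planned number of fractions has not been delivered by the fourth calendar day after the planned last-fraction date, for any reason, including permanent discontinuation or death. For patients who complete the course this equals the present threshold, since finishing on the fourth day is an overrun of 4 and finishing later is 5 or more. Keep the present rule as a sensitivity analysis. In section 6.1, state whether 25% and 10% include permanent stops.

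The cost is one paragraph, plus a matching line in the SAP. The rule needs planned and delivered fraction counts as well as the dates. The case report form in Appendix 5, as reproduced, shows no such fields, so their source should be named. The event becomes a composite of delay and non-completion. Its rate may rise in both arms, and power will depend on how stops split between arms, as shown above. The change affects scoring only and implies nothing about when treatment should be stopped.

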### 4.2 QoL

Assessed using the EORTC QLQ-C30 and EORTC QLQ-H&N35 questionnaires.

### 4.3 Nutritional Status

Evaluated using NRS 2002 and PG-SGA.

### 4.4 Psychological Status

Assessed using the DT, PHQ-9, and HADS.

### 4.5 Rehospitalization

Defined as any unplanned hospital admission during the follow-up period for reasons unrelated to anti-tumor treatment.

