## 1. Background

Radiotherapy (RT) serves as a principal therapeutic modality for malignant head and neck tumors. Cumulative evidence indicates that unplanned radiotherapy interruption is a robust independent predictor of poorer survival outcomes across various cancers. This association is particularly more pronounced in patients with head and neck malignancies, where studies indicate that each day of interruption reduces tumor control by at least 1%. Notably, between 41.6% and 63.6% of patients with head and neck cancer experience such interruptions, primarily due to compromised nutritional status and psychological distress. Research indicates that 37.9% of cancer patients receiving radiotherapy experience weight loss during treatment. A study based on the Patient-Generated Subjective Global Assessment (PG-SGA) scale revealed that the incidence of malnutrition in patients with malignant head and neck tumors rose significantly from 24% before radiotherapy to 88% afterward. Moreover, 71.5% of patients with malignant head and neck tumors experience varying degrees of anxiety, depression, and other psychological disorders. This establishes a detrimental cycle between nutrition and psychological well-being, which may interrupt radiotherapy and impact patients' quality of life (QoL).

In China, patients often receive their RT in an outpatient setting, and nutrition clinics and psychological clinics are available only in some larger-scale hospitals, which restricts patients' access to nutritional and psychological support. Simultaneously, both oncologists and a majority of cancer patients often underestimate the importance of nutritional and psychological care, resulting in delayed interventions. These circumstances can lead to the interruption of RT, with reported rates ranging from 23.5% to 42.5% for head and neck tumors. Radiotherapy interruption directly undermines tumor control efficacy, thereby jeopardizing long-term survival outcomes in patients.

Therefore, the SHINE-MDT (comprising oncology nurse specialists, radiation oncologists, medical oncologists, dietitians, psychotherapists, and rehabilitation physicians) was established to provide nutritional, psychological, and rehabilitated support for patients with

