## 2. Objectives of the research

- **Primary Objectives:** To investigate the effect of SHINE-MDT on the rate of radiotherapy interruption.
- **Secondary objective:** To evaluate patients' QoL, nutritional status, psychological well-being, rehospitalization rate, and tumor response.
  - To investigate the impact of SHINE-MDT on patients' QoL based on the European Organization for Research and Treatment of Cancer (EORTC) Quality-of-life Questionnaire Core 30 (EORTC QLQ-C30) and Head and Neck Cancer Module (EORTC QLQ-H&N35).
  - To investigate the effect of SHINE-MDT on patients' nutritional status based on the Nutritional Risk Screening 2002 (NRS 2002) and PG-SGA.
  - To investigate the impact of SHINE-MDT care on patients' psychological status based on the Distress Thermometer (DT), Patient Health Questionnaire-9 (PHQ-9), and Hospital Anxiety and Depression Scale (HADS)
  - To investigate the impact of SHINE-MDT on the rehospitalization rate.
  - To investigate the effect of SHINE-MDT on tumor response according to RECIST version 1.1.

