## 5. Adverse Events and Serious Adverse Events

### 5.1 Adverse Events (AE)

An AE is an adverse medical event that occurs in clinical study subjects after receiving treatment but is not necessarily causally related to the treatment. Adverse events also include pre-existing diseases that increase in frequency and severity during the study.

➤ **AEs do not encompass the following situations:**

1. Conditions, diseases, or laboratory test abnormalities pre-exist or are detected before screening and do not further deteriorate.
2. Instances where adverse medical events did not occur (such as hospitalization due to elective surgery, social reasons, and/or personal convenience)

➤ **Expected Adverse Events of the Study:**

The expected adverse events in this study primarily involve those associated with radiotherapy and chemotherapy for head and neck tumors. The severity of acute radiotherapy reactions and chemotherapy-related adverse events will be evaluated using the RTOG acute radiation morbidity scoring criteria, RTOG/EORTC late radiation morbidity scoring scheme, and the NCI CTCAE Version 5.0.

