## 5.2 Serious Adverse Events

A serious adverse event (SAE) is an adverse event that meets any of the following criteria:

1. Causing death;
2. Life-threatening;
3. Requires hospitalization or extended hospitalization;
4. Causing permanent or severe disability/incapacity;
5. Causing congenital anomalies/congenital disabilities;
6. Other significant medical events.

Significant medical events that cannot result in death, life-threatening situations, or hospitalization can also be considered SAEs related to the treatment if they may harm the subject. Based on appropriate medical diagnosis, medical or surgical intervention should be provided to prevent any of the outcomes defined above.

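### As worded, the rehospitalization endpoint leaves out unplanned admissions for treatment toxicity, which are among those SHINE-MDT is most likely to reduce, and rests on a relatedness judgement with no stated rule

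*Protocol*

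**What the plan says.** Section 2 of the protocol lists rehospitalization among the secondary objectives: "To investigate the impact of SHINE-MDT on the rehospitalization rate". Section 4.5 supplies the whole definition: "any unplanned hospital admission during the follow-up period for reasons unrelated to anti-tumor treatment". It does not say who judges relatedness or by what criteria, and it gives no start or end for the follow-up period.

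Four other places bear on it:

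- Section 1 reports that malnutrition in head and neck patients "rose significantly from 24% before radiotherapy to 88% afterward".
- Section 3.2 says of the intervention: "This team provided direct and prompt nutritional, psychological, and rehabilitation interventions tailored to the patient's needs". Its rehabilitation component includes swallowing therapy for dysphagia.
- Section 5.1 states: "The expected adverse events in this study primarily involve those associated with radiotherapy and chemotherapy for head and neck tumors".
- Two neighbouring definitions carry no cause filter. The primary endpoint in section 4.1 counts interruption "regardless of the causes for interruption", and section 5.2 makes an adverse event serious if it "Requires hospitalization or extended hospitalization", whether or not it is related to treatment.

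**The concern.** The protocol expects the main harms to come from radiotherapy and chemotherapy, and it builds an intervention to manage the nutritional and functional consequences. An admission because a patient cannot eat or swallow after radiotherapy is a natural thing for that intervention to prevent. Under section 4.5 it does not count if it is judged related to treatment.

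Two things are at stake. First, part of any real reduction in unplanned admissions would fall outside the endpoint, so a null result could be misread as no effect on admissions. Second, whether an admission counts depends on a causal judgement that is often unclear here, since nutritional decline can come from the tumour, the treatment or both. Without a rule, similar admissions may be classified differently.

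**Working it through.** **1. Is the sample size affected?** No. Section 6.1 uses 25% versus 10%, one-sided alpha 0.025, power 0.8 and 5% dropout. With pooled variance under the null and no continuity correction:

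n = [1.960·√(2·0.175·0.825) + 0.842·√(0.25·0.75 + 0.10·0.90)]² / 0.15² = 99.5, so 100 per arm.

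100/0.95 = 105.3, so 106 per arm and 212 in total, against 214 stated. This agrees closely, and rehospitalization does not enter it.

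**2. What the definition keeps and drops**

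| Unplanned admission during follow-up | Counted under section 4.5, read literally? |
|---|---|
| Toxicity of radiotherapy or chemotherapy | No |
| Nutritional failure attributed to that toxicity | No |
| Nutritional failure attributed to the tumour or another cause | Yes |
| Psychological reasons unrelated to treatment | Yes |
| Other unrelated illness | Yes |

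No other section brings the first two rows back. They are the rows that sections 1, 3.2 and 5.1 point to as expected morbidity and as a target of the support.

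**3. Is relatedness governed elsewhere?** The causality table in section 5.4 is an adverse drug reaction form with five grades, including a possibly-unrelated grade and an undeterminable one. Nothing links it to section 4.5, and no cut-off says which grades make an admission unrelated. The randomization and blinding text in section 3.2 describes allocation concealment but no blinded assessor. Section 3.3 treats the two arms in separate buildings and time blocks.

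**4. Illustrative size.** The protocol gives no rehospitalization rate, so every rate below is an assumption.

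*(a) Same relative effect in all admissions.* Exact rejection probability of the pooled z-test, 107 per arm, one-sided 0.025:

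- All unplanned admissions, 20% versus 10%: 0.546.
- Only those meeting the definition, 6% versus 3%: 0.164. The relative reduction is still one half, but the absolute difference falls from 10 to 3 percentage points.
- If the counted admissions are not affected at all, 6% versus 6%: 0.024, which is simply the type I error rate. This case assumes its own answer.

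*(b) Effect confined to treatment-related admissions.* Let T be the control rate of all unplanned admissions and s the treatment-related share, and let SHINE-MDT halve only the related part. The all-cause contrast is T versus T(1 − s) + Ts/2. The contrast under section 4.5 is T(1 − s) in both arms, again by construction. With 101 evaluable per arm (107 × 0.95 = 101.65, rounded down) and one-sided 0.025, normal-approximation power for the all-cause contrast is:

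| T | s | All-cause rates | Power | Section 4.5 rates |
|---|---|---|---|---|
| 15% | 25% | 15.0% v 13.1% | 0.06 | 11.2% v 11.2% |
| 20% | 50% | 20.0% v 15.0% | 0.15 | 10.0% v 10.0% |
| 30% | 75% | 30.0% v 18.8% | 0.46 | 7.5% v 7.5% |

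The true loss depends on how the effect splits between counted and uncounted admissions, which the protocol cannot tell us. Power is modest even for the all-cause endpoint.

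**The case against.** The strongest objection is that the clause may only be meant to exclude admissions made in order to give anti-tumour treatment, such as a chemotherapy cycle. That reading is possible. It is largely redundant, because scheduled treatment admissions are already removed by the requirement that the admission be unplanned. It is not wholly redundant, since a rescheduled cycle could be an unscheduled admission. But section 4.5 speaks of the reason for admission, not its purpose, and a site following the words would discard toxicity admissions. The sentence needs changing on either reading.

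Several stronger inferences are tempting and do not stand:

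- *That the endpoint cannot show any benefit.* Psychological admissions, and nutritional ones attributed to other causes, still count, and SHINE-MDT could reduce them.
- *That unblinded investigators will classify admissions differently by arm.* The protocol does not say who classifies or whether that person knows the arm. Absence of described blinding makes this a risk, and its direction cannot be inferred.
- *That toxicity admissions during radiotherapy are lost because of the relatedness clause.* Section 3.2 uses follow-up for visits at 1, 2, 3 and 6 months after treatment. On that usage, admissions during radiotherapy are already outside the window.

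It is also fair to say that this is one secondary endpoint, not sized under any definition. That limits the weight of the point but does not remove it.

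**Conclusion.** The point holds as a flaw in the definition of one secondary endpoint. The protocol does not merely leave a rule open: it states one that, taken literally, removes a group of admissions the intervention is particularly likely to reduce, and makes counting depend on an ungoverned judgement. As a measure of SHINE-MDT's effect on unplanned admissions, the result would be diluted toward no difference, and a null finding could not be read as no effect.

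This rests on the literal reading of section 4.5 and on the protocol's own account of expected morbidity. The direction of the dilution assumes that SHINE-MDT prevents at least some treatment-related admissions. Its size is unknown. The primary endpoint, sample size and other secondary endpoints are untouched. The definition should be corrected, but the trial's main conclusion does not depend on it.

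**What to change.** Redefine rehospitalization in section 4.5 as any unplanned hospital admission, for any cause, during the follow-up period, excluding only admissions made to deliver anti-tumour treatment. Report toxicity-related admissions, and the subset meeting the present definition, as components. For those components, name who assigns the cause and by what rule, preferably without knowledge of the arm.

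State the start and end of the follow-up period. If the radiotherapy period is to be included, present that as a separate change with its own reason, because it alters what is counted independently of cause.

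The text change is one sentence, but there is some data cost. The case report form shown in Appendix 5 has no field for admissions or their cause, so these must come from serious adverse event or hospital records. Section 5 gives no collection period for serious adverse events, and section 5.1 does not treat hospital stays for social reasons or convenience, without an adverse medical event, as adverse events. Safety reports alone may therefore be incomplete. Much of the protocol is in the past tense. If data are already collected, the redefinition must be disclosed as post hoc and shown beside the result under the current definition.
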